### Statistical analysis

Statistical analysis will be conducted using SAS software (version 8.2, SAS Institute, Cary, NC, USA). All tests will be two-tailed with *P* values of less than 0.05 considered statistically significant.

Descriptive statistics will be presented for each group as the mean ± standard deviation and all enumeration data will be presented as constituent ratio and rate in the outcomes from baseline to each time point. Changes in differences between groups in the primary and secondary outcomes, before and after treatment and during the follow-up period (at 4 weeks and 12 weeks), will be analyzed using repeated measures ANOVA or a rank-sum test.

Changes in effect sizes between pre- and post-intervention will be performed using the Wilcoxon test and chi square test. The effect size will be evaluated with safety set (SS), full analysis set (FAS), per-protocol set (PPS) and cost-effectiveness analysis. Demographic and CHC characteristics, as well as baseline data, will be analyzed using the FAS to assess the baseline and CHC comparability between groups. The primary analysis of the data will be undertaken using FAS with the principle of intention-to-treat and the PPS. The secondary analysis of the data will be undertaken using PPS. To account for missing data, multiple imputation of missing follow-up measures will be performed per the methods used for missing data [41]. The PPS will be used to assess adherence, the SS to assess adverse events and the cost-effectiveness analysis to assess health economics.

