**Method/design:**

This will be a randomized controlled clinical trial with blinded assessment. There will be a 4-week intervention utilizing rehabilitation protocols from traditional Chinese medicine and conventional therapy. Follow-up will be conducted for a period of 12 weeks. A total of 722 participants with knee osteoarthritis will be recruited. Participants will be randomly divided into two groups: experimental and control. Primary outcomes will include range of motion, girth measurement, the visual analogue scale, and results from the manual muscle, six-minute walking and stair-climbing tests. Secondary outcomes will include average daily consumption of pain medication, ability to perform daily tasks and health-related quality-of-life assessments. Other outcomes will include rate of adverse events and economic effects. Relative cost-effectiveness will be determined from health service usage and outcome data.

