## Methods/design

### Study design

This will be a cluster randomized controlled trial with blinded assessment (Figure 1). The trial will comprise a 4-week intervention, using the CTCMRP and conventional therapy (CT), and a 12-week follow-up period. The protocol will be conducted at CHCs run by the Affiliated People’s Hospital of Fujian University of Traditional Chinese Medicine (Fujian province, China), the Comprehensive Traditional and Western Medicine Hospital of Guangdong province (Guangdong province, China), the Chengdu Military Region General Hospital of the Chinese People’s Liberation Army (Sichuan province, China) and the First Affiliated Hospital of Guangzhou University of Traditional Chinese Medicine (Guangdong province, China). To include a broad range of patients, this protocol includes CHCs in different areas. Fujian University of Traditional Chinese Medicine (FJTCM) is responsible for training and supervising rehabilitation therapists at all clinical sites. The evidence-based medicine center, which will be used for documentation and data analysis, is an independent site that performs data monitoring, randomization and statistical evaluation and will be blind to the intervention. Patients will be recruited through CHC outpatient clinics. The Human Research Ethics Committee at Fujian University of Traditional Chinese Medicine (Fujian province, China) approved the study.

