### Randomization and allocation

Following an epidemiological survey, the CHC randomization list for this study will be computer generated using SAS software (Version 8.2, SAS Institute, Cary, NC, USA) and concealed at an independent evidence-based medical center. Employees at the medical center will also be blinded to the intervention. Treatment allocation will start when it has been determined that a study participant meets the inclusion criteria and has signed the informed consent.

The CHC randomization program will assign subjects to each group and each participant’s group number will be displayed (CTCMRP versus CT rehabilitation) on the back of the form. Baseline measurements will not be viewed until the end of the study to ensure blinded assessment. The allocation list will be protected and held by FJTCM. In the event of an emergency, the individual’s randomization code and group allocation can be identified. Therapists at each participating CHC will provide treatment, as usual, to patients who are not eligible or willing to participate.

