### Sample size

In cluster randomized trials, the inspection efficiency comes from the random unit number (cluster number) rather than the size. There are two important factors when estimating the sample number: (1) The number within each cluster group and (2) the intraclass correlation coefficient estimate. The total number of subjects (*n*) from all of the CHCs was calculated according to the estimation formula [23]:

$$n=\frac{{\left(\mu_{\alpha }+\mu_{\beta }\right)}^{2}\left[\pi_{1}\left(1-\pi_{1}\right)+\pi_{2}\left(1-\pi_{2}\right)\right]\left[1+\left(m-1\right)\rho \right]}{{\left(\pi_{1}-\pi_{2}\right)}^{2}}$$

In a trial test of this protocol, the curative effect rate after rehabilitation of KOA was 70% in the control group (*π*_1_) and 82.3% in the experimental group (*π*_2_); this will be used as the main index. The number of qualified participants recruited from each CHC (*m*) will not be less than 17. Prior data indicate that the intra-CHC correlation coefficient (*ρ*) is likely to be, at most, 0.020, and*μ*_*α*_ = 0.05 and *μ*_*β*_ = 0.10.

There are 38 CHCs. Based on the formula, each group (control and experimental) will comprise 323 participants. A total number of 722 subjects will be included to allow for a dropout rate of 10%.

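### The between-group tests, as named, take no account of the community health centre, although the stated design and sample size make it the randomised unit

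*Protocol article*

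**What the plan says.** Four parts of the protocol article bear on this.

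- **Study design:** "This will be a cluster randomized controlled trial with blinded assessment".
- **Sample size:** the section states that "the inspection efficiency comes from the random unit number (cluster number) rather than the size". It multiplies a two-proportion formula by 1 + (m − 1)ρ, with m at least 17 and 38 CHCs. It also gives a source for the clustering parameter ("Prior data indicate that the intra-CHC correlation coefficient" is the opening of that sentence) and puts its likely maximum at 0.020. The result is 323 per group, and 722 in total after allowing for 10% dropout.
- **Statistical analysis:** differences between groups in the primary and secondary outcomes over time "will be analyzed using repeated measures ANOVA or a rank-sum test". Wilcoxon and chi-square tests are named for pre-to-post effects. All tests are two-sided at 0.05. CHC appears here only for describing CHC characteristics and checking comparability at baseline.
- **Wording that points to another unit:** the Abstract says "Participants will be randomly divided into two groups: experimental and control". Randomization and allocation first says "the CHC randomization list for this study will be computer generated using SAS software", then "The CHC randomization program will assign subjects to each group", with allocation starting once a participant is eligible and has consented.

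**The concern.** When whole CHCs are allocated, participants from one CHC share therapists, setting and catchment, so their outcomes are correlated. A test that counts each participant as independent then understates the variance of the treatment difference. Repeated measures ANOVA allows for correlation between visits of the same participant, but that is a different correlation from the one between participants of the same CHC. Ordinary rank-sum and chi-square tests on participants allow for neither.

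The article thus enlarges the trial because of clustering and then names tests that take no account of it. At stake is the error rate of the between-group efficacy comparisons: P below 0.05 would not mean a 5% test, and confidence intervals would be too narrow.

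**Working it through.** **Inputs.** From Sample size: rates 70% and 82.3%, m = 17 (minimum), ρ = 0.020 (upper value), 38 CHCs, 323 per group, 722 in total. The values 0.05 and 0.10 given there are read as the two-sided α and β. From Statistical analysis: two-sided 0.05. Assumed: 19 CHCs per arm and equal cluster sizes. The recruited size per CHC is 722/38 = 19.

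**Step 1: reproduce the plan's sample size.**

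n per group without clustering = (1.960 + 1.282)² × [0.70 × 0.30 + 0.823 × 0.177] / (0.123)² = 247.0

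Design effect = 1 + (17 − 1) × 0.020 = 1.32

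n per group with clustering = 247.0 × 1.32 = 326.1

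The stated figure is 323, which is also 38 × 17/2. The difference from 326 is 0.9%. The unclustered figure of 247 does not come close, so the stated size depends on the design effect. For dropout, 646/0.9 = 718, against the stated 722 = 38 × 19.

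**Step 2: standard errors if clustering is ignored.**

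Naive SE / correct SE = 1/√DE

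- 17 per CHC, DE 1.32: 1/√1.32 = 0.870, so the naive SE is 13% too small and the correct one is 15% larger.
- 19 per CHC, DE 1 + 18 × 0.020 = 1.36: 1/√1.36 = 0.857, so the naive SE is 14% too small and the correct one is 17% larger.

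**Step 3: true type I error of a nominal two-sided 5% test.**

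True α = 2 × [1 − Φ(1.96/√DE)]

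| ICC | 17 per CHC | 19 per CHC |
|---|---|---|
| 0.005 | DE 1.08: 5.9% | DE 1.09: 6.1% |
| 0.01 | DE 1.16: 6.9% | DE 1.18: 7.1% |
| 0.020 (protocol's upper value) | DE 1.32: 8.8% | DE 1.36: 9.3% |

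**Step 4: check by simulation.** Binary outcomes were drawn from a beta-binomial model with ICC 0.020, 19 CHCs per arm, no treatment effect, a common rate of 0.70 or 0.7615, and 100,000 runs. The participant-level test rejected in 8.7-8.8% of runs (17 per CHC) and 9.3-9.4% (19 per CHC). A t-test on the 38 CHC proportions (36 df) rejected in 4.9-5.0%. With rates of 70% and 82.3%, the power of that t-test was about 88% at 17 per CHC and 90% at 19.

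**Step 5: width of corrected intervals.** Replacing the naive SE widens intervals by 15-17%. Using t on 36 df as well (2.028 instead of 1.960, a factor of 1.035) gives 1.149 × 1.035 = 1.19 to 1.166 × 1.035 = 1.21, that is 19-21%.

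**The case against.** The strongest objection concerns the unit of allocation. The Abstract and part of Randomization and allocation speak of participants or subjects being assigned, after eligibility and consent. If individuals were randomised within CHCs, the inflation calculated here would not arise in this form. That stands as a condition on the result. It does not clear the article, because the cluster label in Study design and the design effect in Sample size would then be wrong.

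A second objection is that an article condenses, and that a repeated measures model can carry a CHC term or a rank test can be run on CHC summaries. Hence the claim is limited to the tests as named. But the article is not silent: it lists specific tests, and nothing in that list reflects the clustering on which its sample size depends.

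Three stronger readings are tempting and are not supported.

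- A reader might carry 8.8-9.3% over to every outcome. The calculation is for the curative-effect rate. The ICCs of the other outcomes are not given, and stable differences between CHCs partly cancel in changes from baseline.
- A reader might treat 8.8-9.3% as the central estimate, or extend the range to an ICC of 0.05 (14-16%). The article gives 0.020 as the likely maximum, so 8.8-9.3% is the upper end on its own terms.
- A reader might fault the imputation for omitting CHC. The article says only that "multiple imputation of missing follow-up measures will be performed per the methods used for missing data" and cites a source that is not at hand. What the imputation model contains is properly left to a fuller document.

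**Conclusion.** The stated analysis conflicts with the stated design, and this must be corrected before the data are analysed. Conditional on CHC allocation, the nominal 5% test of the curative-effect rate is in truth a test at up to about 9%, and at about 6-7% if the ICC is 0.005 to 0.01. Any positive ICC moves the error above 5%.

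The figures rest on equal cluster sizes and an even split of the 38 CHCs, which the article does not state outright; unequal sizes would tend to increase the inflation. The direction of the problem is the same for the other between-group outcomes wherever their ICC is positive, but its size cannot be given from the documents.

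**What to change.** 1. **State the unit of allocation.** Reconcile the Abstract and Randomization and allocation with Study design and Sample size. If individuals are in fact randomised within CHCs, the cluster label and the design effect are what need correcting.
2. **If the CHC is the unit, replace the named between-group tests.** For continuous outcomes, use a linear mixed model with a random effect for CHC and repeated measures within participant. For the curative-effect rate, use GEE clustered on CHC or a mixed logistic model, with a small-sample correction, or a t-test on the 38 CHC proportions with 36 df.

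The cost is wording only: no further data or patients, and Trial status says that recruitment is still going on. Confidence intervals become wider by the amounts in Step 5. Power stays close to the planned 90%, because the sample size already allows for clustering.

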### Baseline measurements

Baseline descriptive data will be obtained via a questionnaire (Table 1).

**Table 1 T1:** Baseline descriptive data

**Data**	**Content**
General data	Agent of the person who conducted test, test start date, the patient’s address, name of accompanying family members and the patient’s telephone number
Demographic data of subject	Gender, age, nationality, level of education, profession, height and weight
Assessment of knee before test	Visual analogue scale (VAS), knee girth, knee’s range of motion (ROM), manual muscle test (MMT), stair-climbing ability, walking distance, comprehensive effect, average daily amount of non-steroidal anti-inflammatory drugs taken, activities of daily living (ADL), quality of life (QOL), safety assessments and economic evaluation
Other	Complications, medication use, previous treatment and duration of KOA symptoms

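### The between-arm change comparisons omit the collected baseline values as covariates, which costs precision, and the added pre/post tests, read literally, cannot compare the two active arms

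*Protocol article*

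**What the plan says.** The Statistical analysis section has two consecutive sentences on efficacy testing.

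- The first covers "Changes in differences between groups in the primary and secondary outcomes, before and after treatment and during the follow-up period" and says that these "will be analyzed using repeated measures ANOVA or a rank-sum test". It names no covariate and no adjusted model.
- The second reads "Changes in effect sizes between pre- and post-intervention will be performed using the Wilcoxon test and chi square test". It does not say whether arms are being compared. It does not mark the tests as descriptive, and the general rule in the same section applies to them: "All tests will be two-tailed with *P* values of less than 0.05 considered statistically significant".

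Under Baseline measurements, the Table 1 row headed "Assessment of knee before test" lists "Visual analogue scale (VAS), knee girth, knee’s range of motion (ROM), manual muscle test (MMT), stair-climbing ability, walking distance, comprehensive effect", followed by drug use, activities of daily living and quality of life. The primary and secondary measures are therefore all listed for collection before treatment. Apart from entering the change comparisons, the one stated analytic use of baseline data is "to assess the baseline and CHC comparability between groups".

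**The concern.** There are two separate matters.

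1. The between-arm analysis uses change from baseline but does not condition on the baseline value. A change score subtracts the whole baseline value, while the follow-up value is predicted by only a fraction r of it (on a common SD scale). The surplus adds noise. When the arms happen to differ at baseline, it also moves the estimate, because the arm that starts worse tends to improve more for reasons unrelated to treatment.
2. Read as written, the second sentence tests each group's before-to-after change. Both arms receive active rehabilitation, and the sample size section expects a 70% curative effect rate in controls. Significant improvement in both arms is to be expected and says nothing about which treatment is better. If the chi-square test were applied to before and after categories of the same patients, its independence assumption would also fail.

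At stake are avoidable loss of precision on the continuous outcomes, and within-arm P values that could be reported as if they were evidence of efficacy.

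**Working it through.** **The plan's own figure.** Inputs from the Sample size section: rates 0.70 and 0.823, m = 17, ICC 0.020. The printed 0.05 and 0.10 are read as error rates (two-sided alpha, 90% power).

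- Design effect: 1 + (17 − 1) × 0.020 = 1.32.
- Variance term: 0.70 × 0.30 + 0.823 × 0.177 = 0.3557.
- n per group: (1.960 + 1.282)² × 0.3557 × 1.32 / 0.123² = 326.

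The article states 323, which is 19 × 17 and within 1% of this. The total of 722 is 38 × 19; 646/0.9 gives 718. The calculation compares two proportions and has no baseline term, so nothing below changes it.

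**Precision.** The article gives no outcome SD and no r, so r is assumed. Take one follow-up, equal variances (set to 1) and independent patients. The variance per patient is then 2(1 − r) for a change score and 1 − r² after baseline adjustment, so the ratio is (1 − r²)/[2(1 − r)] = (1 + r)/2.

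| assumed r | change score | adjusted | ratio | SE reduction | extra patients a change score needs | power after adjustment if 90% on change |
|---|---|---|---|---|---|---|
| 0.3 | 1.40 | 0.91 | 0.65 | 19% | 54% | 98.0% |
| 0.5 | 1.00 | 0.75 | 0.75 | 13% | 33% | 96.3% |
| 0.7 | 0.60 | 0.51 | 0.85 | 8% | 18% | 94.0% |
| 0.8 | 0.40 | 0.36 | 0.90 | 5% | 11% | 92.7% |

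SE reduction is 1 − √ratio; extra patients is 1/ratio − 1.

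**Baseline imbalance.** If the arms differ by D at baseline, a change-score estimate has expectation (true effect) + rD − D, so it is off by −(1 − r)D. Averaged over randomization D is zero. As a guide to chance size, assume that the ICC of 0.020 also holds for baseline measures: the SE of D is √(2 × 1.32/323) = 0.09 SD, a 95% range of about ±0.18 SD. At D = 0.18 the shift is 0.13, 0.09 and 0.05 SD for r = 0.3, 0.5 and 0.7. Under the same model, baseline adjustment removes it.

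**Pre/post tests.** In a simulation with 323 patients per arm, both arms improved by the same 0.3 SD (assumed; r = 0.5, no clustering, 2,000 runs). The within-arm Wilcoxon test was significant in 99.8% and 99.95% of runs for the two arms. The between-arm rank-sum test on change rejected in 5.5%, about its nominal level. Within-arm significance therefore carried no information on the contrast between arms.

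**The case against.** The strongest reply is that the plan already compares the arms. The sentence before the quoted one does so for all primary and secondary outcomes. A group-by-time ANOVA or a rank-sum test on change addresses the arm contrast and is unbiased on average under randomization. This stands. A reader might infer that efficacy rests on pre/post tests, or that baseline imbalance passes straight into the estimate. The article supports neither: the pre/post tests are additional, and a change score removes the baseline value, leaving only the −(1 − r)D component.

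Secondly, the quoted sentence is ambiguous. The Wilcoxon test is not specified as signed-rank. The curative effect rate, which the Sample size section calls the main index, is built from each patient's percent change and so has one value per patient. A chi-square test on it would naturally compare arms. (Table 1 lists the comprehensive effect among baseline items, but as defined it cannot be computed before treatment.) This also stands, so it cannot be said that the plan applies an invalid chi-square test to paired data, only that the literal wording would.

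Thirdly, a covariate list may properly be left to an analysis plan that is not shown. That is fair as to the list. The article does, however, name the methods, and those named are unadjusted.

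Lastly, the (1 + r)/2 ratio is for a simple change score with one follow-up and independent patients, whereas the plan has several visits, a rank-based option and clusters. The ratio is a guide to size and not a forecast. Nor does baseline adjustment cure differential recruitment by CHCs beyond what the measured baseline value captures.

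**Conclusion.** The point holds as one of precision and clarity. The stated between-arm methods are valid on average but give up precision that data already being collected would supply. For a simple change score, adjustment would cut the standard error by 8% to 19% for r between 0.7 and 0.3, and by 5% at r = 0.8. All values of r are assumptions. The gain concerns the continuous outcomes only.

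A reader might take the 54%, 33% and 18% figures to mean that the trial is too small. They do not: 323 per group and 722 in total come from two proportions and do not change.

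The pre/post sentence, read literally, cannot distinguish two active arms. Whether that reading is intended cannot be settled from the article, so the sentence needs rewording whichever is meant.

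**What to change.** - For each continuous outcome, replace the ANOVA or rank-sum comparison with a model of the post-baseline visits containing arm, visit, arm-by-visit and the participant's baseline value, with CHC as the cluster. Report the adjusted between-arm difference with a 95% CI.
- Label any pre/post tests as descriptive and keep them out of the efficacy conclusions.
- State that the chi-square comparison of the curative effect rate is between arms, and give it in a cluster-adjusted form.

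CHC enters the model because CHCs are the unit of randomization; that requirement stands apart from the precision argument here. The cost is analysis wording only. No new data, visits or patients are needed, and the sample size stays as stated.

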## Discussion

KOA is a major public health problem and this project, funded by the State Administration of Traditional Chinese Medicine, has two aims. First, the curative effect of CTCMRP for KOA rehabilitation will be assessed and CTCMRP will be examined to develop a SRPTCM for KOA rehabilitation in China and worldwide. Secondly, self-management for KOA patients will be improved and their financial burden reduced.

In this study, the rehabilitation therapists will undergo rigorous training and accreditation to administer the CTCMRP intervention. Regular meetings will be held throughout the study to exchange views. The outcome measures will include self-reported measures of pain, the SF-36, QOL and activities of daily living. Knee ROM, the 6 MW test, the stair-climbing test and the comprehensive effect will assess functional performance, strength and physical activity levels. In addition, a health economic assessment will be used to justify the cost-effectiveness of treatments in the current economic climate and a safety assessment will be done to assess adverse events.

The biggest limitation of this protocol is that there is no placebo control and it is not double-blinded. However, the evidence-based medicine center will be blind to the intervention to decrease possible bias. The study also lacks long-term follow-up and evaluation. The 4-week intervention period reflects what is done in actual clinical practice and is long enough to test whether a rehabilitation modality is effective in the short term and whether the efficacy is sustained during the follow-up period. Due to ethical considerations, non-steroidal anti-inflammatory drugs will be permitted as required.

If successful, this project offers a low-cost solution for efficiently linking millions of hospitalized KOA patients with effective outpatient treatment. CTCMRP rehabilitation therapy for KOA can be done in a CHC or at home instead of in a high-grade hospital, thus reducing the financial burden for the patient.

